### Data handling

Data are handled confidentially and anonymously. Each student’s data are stored under a unique eight-digit code that is not related to the student’s name, initials or birth date. The key to the codes remains at the school with the director. All research data (i.e., data with codes) are stored on a secured server computer at the Leyden Academy. The school (code key) and the Leyden Academy (data) are physically separated. The handling of data complies with the General Data Protection Regulation [83]. The data will be stored for 10 years. In all reporting no codes will be reported.

The database will be managed in Microsoft Excel 2016 and IBM SPSS Statistics, Version 23.0. The results of the Activ8® Professional activity tracker are collected with the Activ8® Professional recording tool; the computer test data from the executive functioning tests are first collected with the Inquisit 4 Computer Software. Data collected on paper forms are checked and data entry is performed by the Data Manager at Leyden Academy. All authors ([name], [name], [name]) are given access to the full dataset.

### Statistical analysis

The statistical analysis will be conducted in SPSS. A two-tailed significance level of .05 will be used for all tests.

Summary statistics for the baseline measures and participant demographics for both groups will first be examined. Dependent on the variable, the means, medians or frequencies will be compared between both groups using a two-sample T-test, a Mann-Whitney U test or chi-square test, as appropriate.

Outcome data obtained from all students will be included in the data analysis, and data will be analyzed as per group allocation. In our statistical analysis the longitudinal and multilevel structure of the data are acknowledged and will be taken into account in achievement growth modeling. For this, mixed modeling will be used, because this specifically allows for the analysis of repeated measures and nested data. Furthermore, missing data are better handled in mixed modeling. We will first determine the growth (longitudinal changes) for the different outcome measures on an individual and on a group level. In determining the proportion of variance explained by group allocation (i.e., sit-to-stand or regular desks) for sitting time as well as for academic performance (i.e., the primary outcome measures), explanatory variables such as age, gender and baseline outcomes will be added to the model. We will do this both on an individual and on a group level, also for a number of secondary outcome measures. We will test for significance of the effect of group allocation on a group level.

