### Sample size, power, and non-inferiority

In relation to possible harm to academic performance as an adverse event of long term use of sit-to-stand desks, we will investigate (non-)inferiority, rather than the effectiveness of sit-to-stand desks on measures of academic performance. For this, the 95% confidence interval (CI) and a margin of non-inferiority (the maximum acceptable extent of non-inferiority of an experimental treatment) are relevant. For the following calculations we have used the expected 20 students per group, and the distribution data of academic performance provided by CITO [https://www.cito.com]. Note that the data of the school participating in this study are similar to the data provided by CITO:

$$ \mathrm{We}\ \mathrm{assume}:{\mathrm{n}}_{\mathrm{exp}}={\mathrm{n}}_{\mathrm{con}}=20\ \mathrm{and}\ \mathrm{equal}\ \mathrm{variance} $$

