**Table Taba:** 

	Reading comprehension	Arithmetic	Orthography
Mean	159	214	214
SD	25	26	26
SE diff	7.9	8.3	8.3
95% CI diff	15.8	16.6	16.6
% mean	10	7.8	7.8

This means that for accepting non-inferiority in case μ = 0 or μ > 0, at maximum a difference between the mean scores of both groups of around 10% will be accepted. If μ < 0 (i.e., the mean score of the experimental group is more than 10% lower than the mean score of the control group), non-inferiority will not be accepted.

With regard to the proportion of sitting time (i.e., second primary outcome), we look at the effectiveness of sit-to-stand desks. For these calculations we used the results from the study by Clemes et al. [17]. We used the pooled statistics of the follow-up assessment of the control groups in this study to calculate the 95% CI. Based on these results, chances are small that in this study, with an expected 20 participants in each group, a significant difference in sitting time will be found between groups at the end of the study (i.e., the α-approach). The lower and upper limits of the 95% CI (H_0_) are 59.9 and 70.2 respectively, with an expected mean of 60.3 for the experimental group. However, we may fail to detect a difference when actually there is a difference (i.e., the β-approach). Following similar differences between experimental and control groups in the Clemes et al. [17] study, this probability of failing to detect a difference when actually there is a difference is almost 50% (β = 0.54; power = 0.46).

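### The analysis section names variance explained and a two-tailed test for the primary outcomes, and so does not carry out the protocol's own non-inferiority rule for academic performance

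*Protocol article*

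**What the plan says.** Two sections of the protocol article bear on this.

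Under Sample size, power, and non-inferiority, academic performance is framed as a non-inferiority question: "For this, the 95% confidence interval (CI) and a margin of non-inferiority" are the tools named. The table there gives means and SDs for reading comprehension, arithmetic and orthography. The text after it sets the limit, "at maximum a difference between the mean scores of both groups of around 10% will be accepted", and gives it a direction: non-inferiority is refused if "the mean score of the experimental group is more than 10% lower than the mean score of the control group". Sitting time is treated in the same section as an effectiveness question, without a margin.

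Under Statistical analysis, the plan is mixed modelling of growth. The one quantity named there for expressing the effect of the desks on the two primary outcomes appears in the clause "In determining the proportion of variance explained by group allocation (i.e., sit-to-stand or regular desks) for sitting time as well as for academic performance"; the sentence goes on to add age, gender and baseline outcomes to the model. Two statements on testing complete it: "We will test for significance of the effect of group allocation on a group level" and "A two-tailed significance level of .05 will be used for all tests". The section does not mention non-inferiority, the margin, or a confidence interval for a difference.

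**The concern.** The Background section makes possible harm to academic performance the primary aim. Answering it needs a difference with a sign, in CITO points, and an interval that can be set against the margin. The quantity named in the analysis section is the same for a class that falls behind and a class that pulls ahead by the same amount, and it is not in score points. The accompanying test asks whether the difference is zero. A non-significant result there does not show that a loss of margin size has been excluded, least of all with about 20 children per group. If the analysis section were followed by itself, the trial could report a small share of variance and a non-significant p-value, and these could be misread as no harm when the protocol's own rule would not have been met.

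For sitting time less is at stake: the reader would want to know whether sitting fell and by how much, and variance explained says neither.

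**Working it through.** **Inputs.** From the table under Sample size, power, and non-inferiority: 20 children per group; means 159, 214, 214; SDs 25, 26, 26; SE of the difference 7.9, 8.3, 8.3; 95% CI half-widths 15.8, 16.6, 16.6 (reading, arithmetic, orthography). From the text below it: a margin of about 10%; for sitting time, 95% limits of 59.9 and 70.2 and an expected experimental mean of 60.3.

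**1. The protocol's own figures.** SE = SD × √(2/20).
- Reading: 25 × 0.3162 = 7.91; twice the printed 7.9 is 15.8; 15.8/159 = 9.9%. This agrees with the printed 10%.
- Arithmetic and orthography: 26 × 0.3162 = 8.22, against 8.3 printed; twice 8.3 is 16.6; 16.6/214 = 7.8%. This agrees to within about 1%.

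**2. The margin in points.** Taking 10% of the printed means: 0.10 × 159 = 15.9 for reading; 0.10 × 214 = 21.4 for arithmetic and orthography.

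**3. What variance explained shows at the margin.** For two equal groups whose means differ by D, the between-group variance is D²/4, so R² = (D²/4) / (D²/4 + SD²).
- Reading, D = +15.9 or -15.9: 63.2 / (63.2 + 625) = 9.2%.
- Arithmetic or orthography, D = +21.4 or -21.4: 114.5 / (114.5 + 676) = 14.5%.

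The sign is lost in the squaring, and a single 10% rule becomes two different values of R².

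**4. What the two-tailed test shows.** Suppose an observed reading loss of 12 points with the planned SE of 7.9.
- t = 12/7.9 = 1.52; on 38 df, two-sided p is about 0.14.
- R² = (144/4) / (144/4 + 625) = 36/661 = 5.4%.
- 95% CI: -12 ± 15.8, that is -27.8 to +3.8. The lower limit lies below -15.9, so non-inferiority is not shown.

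**5. How wide the gap is.** Using the printed half-widths, a loss is non-significant up to 15.8 points (reading) or 16.6 points (arithmetic, orthography). The lower limit stays above the margin only for losses below 15.9 - 15.8 = 0.1 points (reading) or 21.4 - 16.6 = 4.8 points (arithmetic, orthography). So any observed loss between about 0.1 and 15.8 points in reading, or between about 4.8 and 16.6 points in the other two tests, is non-significant yet fails the margin.

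**6. Sitting time.** The difference implied by the printed limits is (59.9 + 70.2)/2 - 60.3 = 65.05 - 60.3 = 4.75 percentage points. The SE implied is 5.15/1.96 = 2.63. Read as the SE of a difference, the SD is 2.63/√(2/20) = 8.3; read as the SE of one mean, it is 2.63 × √20 = 11.75. R² is then 5.64/(5.64 + 68.9) = 7.6% or 5.64/(5.64 + 138.1) = 3.9%. Neither figure says whether sitting went down or by how many points.

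**The case against.** The strongest reply is that the document does plan a signed measure. The sample-size section describes a difference in mean scores, a 95% CI, a margin and a direction of harm. The clause on variance explained is subordinate to a statement about adding covariates and is nowhere called the decision criterion. A mixed model with a term for allocation yields a signed coefficient with an interval in score units anyway. And this is a condensed article; the exact contrast to be reported is often left to an analysis plan.

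Much of that stands. A reader might infer that the protocol has no signed effect measure at all for its primary outcomes; the sample-size section contradicts this for academic performance, and it also compares mean sitting proportions. A reader might extend the margin problem to both primary outcomes; the margin belongs to academic performance only. A reader might expect variance explained to swing with the covariate list. That would follow only if a partial R² were meant and baseline were strongly correlated with follow-up, and the protocol states neither. With baseline balanced between the groups, the share of total variance for reading stays at 63.2/688.2 = 9.2%.

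What does not stand is that this is only detail left for later. The analysis section does state a quantity and a test for the primary outcomes, and what it states does not carry out the rule set a few paragraphs before it.

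**Conclusion.** The point holds as a mismatch between two sections. The sample-size section sets a signed, margin-based rule for academic performance; the analysis section names an unsigned, unitless quantity and a two-tailed test of no difference, and neither can apply that rule. At the margin, variance explained is 9.2% (reading) or 14.5% (arithmetic, orthography) for loss and gain alike. For sitting time the defect is limited to the missing direction and unit.

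It should not be inferred that a loss of the full margin would look like a small effect: the protocol sets no benchmark for what counts as small. The supported statement is that the named outputs could be misread.

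Assumptions: 10% is taken of the printed means. The rule is read as comparing the lower confidence limit with the margin, as the reference to a CI suggests, although the wording on refusing non-inferiority speaks of the means themselves. The examples use the protocol's unadjusted SE at one time point with children treated as independent; the mixed-model SE will differ. The sitting difference and its SD are inferred from the printed limits. The 12-point loss is illustrative.

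**What to change.** Add to Statistical analysis a statement that the primary estimate is the mixed-model adjusted difference, experimental minus control, with its 95% CI:
- for academic performance, in CITO points for each of the three tests, with the lower limit compared with the margin from the sample-size section, written in points (15.9 and 21.4 if it is 10% of the printed means);
- for sitting, in percentage points of school time, with no margin.

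State that the two-tailed test does not decide non-inferiority, and keep variance explained as a descriptive line only.

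The cost is a few sentences. The planned SPSS mixed model already produces the estimate and interval, so no new data, software or model is needed. The change should be fixed before the outcome data are examined.

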**Methods:**

Children of two grade-three groups (age 8–9) following regular primary education in Leiden, The Netherlands, were recruited. A coin toss determined which group is the experimental group; the other group is the control group. All children in the experimental group received sit-to-stand desks. They are invited and motivated to reduce sedentary time at school, however, it is their own choice to sit or stand. Children in the control group use regular desks. Otherwise, both groups receive regular treatment. Outcomes are assessed at baseline (T0) and at five follow-up sessions (T1-T5) alternately in winter and summer seasons over three academic years. Primary outcome measures are academic performance, and the proportion of sitting time at school, measured with a 3D accelerometer. Secondary outcome measures are a number of measures related to executive functioning (e.g., N-back task for working memory), health (e.g., height and weight for BMI), and wellbeing (e.g., KIDSCREEN-52 for Quality of Life).

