### Recruitment

Students of two grade-three groups (aged 8–9 years) following regular primary education were recruited from a school in Leiden, The Netherlands, of which the school director initiated this study. At this school there were four grade-three groups. The common group size is 26 to 30 students. The deputy director of the school selected two groups in consultation with the teachers, based on the willingness of the teachers to be involved in the study. All children in both groups were asked to participate. The allocation was only established after baseline assessment (which was after informed consent). In order to be eligible to participate in this study, a student had to meet all of the following criteria:
Follow regular primary education in third gradeHave a signed Informed Consent form to participate; given the age, parents/caregivers should sign the Informed Consent form for their child but the student will be asked to sign one as wellBe physically able to stand without any serious health issues or injuries; note that a student who is normally physically able to stand, but temporarily unable to do so because of a recovery from a temporary injury of trauma, can still participate in this study

Students who object to participate are not included in the study. Examples of objection are (signals of) fear, sadness, and anger. We expected to recruit around 20 students per group. Students who did not participate from the start of the study, but wish to do so at a later moment, are also enrolled at the next moment of testing. Those who terminate their participation before the end of the study are asked for the reason(s) why. Demographics of students that in fact are recruited (and for whom we received written informed consent from themselves and their parents/caregivers) are presented in Table 1.

**Table 1 Tab1:** Participants’ age and sex

	Control group	Intervention group	Total
	(n = 19)	(*n* = 19)	(*n* = 38)
Years of age median [range]	9.0 [8.5 to 10.2]	8.9 [8.5 to 10.3]	8.9 [8.5 to 10.3]
Girls n (%)	10 (52.6)	11 (57.9)	21 (55.3)

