The study also knows some limitations. First, the sample size is most likely too small for detecting a significant difference in sitting time. The downside is that a small sample size limits population estimation and extrapolation of findings. In addition, a possible true effect may be masked by a relatively large variance in our sample (this is the reason why we calculated the probability of failing to detect a difference). On the upside, in the study we use a repeated-measures design instead of the pre-post design that was used in the study by Clemes et al. [17]. This increases the power to some extent. However, given the fact that the primary aim was to assess possible harm to academic performance, the effect of sit-to-stand desks on sedentary time reduction (and the related sample size calculation based on results the study by Clemes et al. [17]) was considered subordinate to the investigation of possible harm to academic performance (and the related non-inferiority calculation). Given the circumstances, we therefore accepted a small sample size, which is around half the sample size of the study by Clemes et al. [17], and we will treat the outcomes with cause.

An additional limitation follows from the group randomization, which is inevitable in studies with school classes. Group randomization has a negative effect on the power of the study. With the proposed statistical analysis (i.e., mixed modeling), we will be able to determine the extent of the negative effect of this design on the power of the study and discuss the consequences.

Furthermore, this study involves only one school. Potential limited external validity and problems with blinding are common limitations in single-center (ic. single-school) studies, which may also apply to this study. We will take these limitations into consideration in our analyses and findings.

The program of “A Good Beginning” started in 2017 and results are expected by the beginning of 2020. The results of this study may provide relevant information to set up a larger scale efficacy trial, possibly with children of different ages (also in secondary education), more schools with different populations, and a protocol focusing primarily on sedentary time reduction.

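### With one class per arm, class-to-class variation cannot be estimated, so the planned mixed model can neither separate desks from class or teacher nor show what group randomisation costs in power

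*Protocol article*

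**What the plan says.** The abstract describes the allocation: "A coin toss determined which group is the experimental group; the other group is the control group". Under Recruitment, both classes come from one school and were picked from its four third-grade classes "based on the willingness of the teachers to be involved in the study". There are therefore two randomised units, one per arm.

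Under Statistical analysis, "mixed modeling will be used, because this specifically allows for the analysis of repeated measures and nested data", and "explanatory variables such as age, gender and baseline outcomes will be added to the model", at both the individual and the group level. The closing sentence is "We will test for significance of the effect of group allocation on a group level", and the general rule is "A two-tailed significance level of .05 will be used for all tests".

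Under Sample size, power, and non-inferiority, "For the following calculations we have used the expected 20 students per group". The table there gives standard errors of 7.9, 8.3 and 8.3 points for the difference in reading comprehension, arithmetic and orthography. The text gives a power of 0.46 for sitting time.

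The Discussion accepts that randomising groups lowers power, then says that through mixed modelling "we will be able to determine the extent of the negative effect of this design on the power of the study".

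**The concern.** Whether group randomisation did damage depends on how much classes differ for reasons other than the desks. That variance can be estimated only from at least two classes in the same arm. Here each arm has one, so the class difference and the desk difference are the same number.

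Two consequences follow. First, the Discussion promises something the model cannot deliver. Second, any interval or p-value that the model does produce describes variation between children only. An ordinary difference between two classes or teachers that arises after baseline could pass for a desk effect or conceal one. This is plausible because the Intervention section gives the teacher an active part in encouraging standing. It bears on both primary outcomes: the sitting-time comparison through the test, and academic performance through the 95% confidence interval set against a margin of about 10%.

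**Working it through.** **1. The plan's own figures.** Inputs: SD 25 / 26 / 26 and 20 children per arm.
- SE of the difference = SD × √(2/20) = 7.91 / 8.22 / 8.22 (stated 7.9 / 8.3 / 8.3).
- Twice the SE = 15.8 / 16.4 / 16.4 (stated 15.8 / 16.6 / 16.6).
- Sitting time: limits 59.9 and 70.2 give centre 65.05 and half-width 5.15; the expected mean of 60.3 gives a difference of 4.75. With the t(38) multiplier, SE = 2.544 and power = Φ(4.75/2.544 - 1.96) = 0.463 (stated 0.46). Multipliers of 2 and 1.96 give 0.454 and 0.440.

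The figures reproduce, to about 1% for the standard errors, from formulas for independent children with no class term.

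**2. Can class variance be estimated?**
- Class-level degrees of freedom: 2 classes - 2 arms = 0.
- The design matrix [intercept, arm] has rank 2. Adding the two class indicators leaves it at 2.
- On simulated data with 19 children per class and residual variance 1, the REML log-likelihood is -20.157 for class variances of 0, 0.05, 0.2, 1 and 5 alike. The SE of the arm effect over the same values is 0.32, 0.45, 0.71, 1.45 and 3.18.
- A randomisation test on two classes has two possible allocations with the same absolute difference, so its smallest two-sided p is 1.0.

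The likelihood is flat, so the SE depends entirely on the class variance that is assumed.

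**3. Size if class is left out.** The article gives no ICC, so the residual ICC ρ is an assumption, shown over a range. With m = 19 children per class (Table 1), the ratio of true to child-level variance is R = 1 + mρ/(1-ρ).
- Two-sided error of a nominal 5% test (sitting time) = 2[1 - Φ(1.96/√R)].
- One-sided error of accepting non-inferiority when the true difference lies at the margin, taking the rule to compare the lower 95% limit with the margin, = 1 - Φ(1.96/√R), nominal 2.5%.

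| Assumed ρ | R | √R | Two-sided | One-sided |
|---|---|---|---|---|
| 0.01 | 1.19 | 1.09 | 7% | 4% |
| 0.02 | 1.39 | 1.18 | 10% | 5% |
| 0.05 | 2.00 | 1.41 | 17% | 8% |
| 0.10 | 3.11 | 1.76 | 27% | 13% |
| 0.20 | 5.75 | 2.40 | 41% | 21% |

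A simulated child-level t-test (40,000 runs) gave two-sided errors of 5% at ρ = 0 and 16 / 25 / 41% at 0.05 / 0.10 / 0.20. A baseline-adjusted simulation (4,000 runs) gave 15 / 24 / 39%.

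**4. Planning illustration only.** Unadjusted, at one time point, with 20 per class and the total SD held fixed, the design effect is 1 + 19ρ. At ρ = 0.05 it is 1.95, and the reading half-width becomes 15.8 × √1.95 = 22.1 points, or 22.1/159 = 13.9% of the mean. This factor differs from R because R = [1 + (m-1)ρ]/(1-ρ): R scales a within-class variance, which is what the trial will estimate, while the design effect scales a total variance.

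**The case against.** **Zero degrees of freedom.** A reader might infer that the planned test certainly has none. The text does not settle this. The article also uses the word group for an arm, and the Statistical analysis section contrasts individual with group growth. The sentence may mean a fixed arm effect in a child-level repeated-measures model, which does have degrees of freedom. This objection stands, but on that reading class variation is simply omitted and the aliasing remains.

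**One test for both outcomes.** A reader might take both primary conclusions to rest on the quoted significance test and apply 17 / 27 / 41% to each. Academic performance is judged by a 95% interval against a margin, so for that outcome the relevant figures are 8 / 13 / 21%.

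**The ICC is assumed.** Correct. No document supports 0.05 as a floor for two same-grade classes in one school after baseline adjustment. At 0.01 and 0.02 the two-sided error is 7% and 10%. Nor is the 22-point half-width a forecast of the trial's interval, because baseline adjustment and repeated measures are planned.

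**Baseline adjustment and repeated measures protect the comparison.** In part: they reduce stable prior differences. They add no class-level degrees of freedom and cannot remove class or teacher influences that arise after baseline.

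**Software would reveal the problem by setting class variance to zero.** It need not. With a flat likelihood, a package may also report a result on child-level degrees of freedom.

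**The limitation is disclosed.** The Discussion admits lower power, a small sample and a single school, and presents the results as input to a larger trial. It does not say that desk and class effects are inseparable, so this mitigates the problem without curing it.

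**Conclusion.** The point holds. Arm and class are aliased by design, class variance cannot be estimated, and the Discussion's claim about measuring the power cost is wrong as written. The published precision and power figures assume that children are independent. These conclusions need no assumed value.

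The size does. Over assumed residual ICCs from 0.01 to 0.20, the sitting-time test's error runs from about 7% to 41% instead of 5%. At 0.05 to 0.20, the error of wrongly accepting non-inferiority at the margin runs from about 8% to 21% instead of 2.5%.

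A reader might go further and call the conclusions exploratory unless they survive a widened interval. The documents offer no ICC on which to base such a rule. On the planning half-widths it would also decide the matter in advance: at 0.05, with an observed difference of zero, reading (22.1 points, 13.9% of the mean) and arithmetic (16.6 × √1.95 = 23.2 points, 23.2/214 = 10.8%) already exceed about 10%.

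**What to change.** 1. Statistical analysis: replace the group-level test with a child-level mixed model (random child effects, fixed arm effect, baseline-adjusted), and state that inference is conditional on these two classes.
2. Discussion: delete the claim that mixed modelling will determine the power cost. State that class variance is not estimable and that desk effects cannot be separated from class or teacher effects.
3. Sample size, power, and non-inferiority: label the standard errors, intervals and power as assuming no class variance.
4. Beside each primary confidence interval, report a sensitivity interval widened by √(1 + mρ/(1-ρ)) over a stated range of assumed ICCs that includes small values. Present it as an aid to interpretation, with no pass/fail rule.

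The cost is wording, one sensitivity line per primary outcome, and less favourable intervals. No new data are needed. The confounding itself cannot be repaired in the analysis; that would take several classes per arm.
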